#### 2.8.2. Secondary Outcomes

Secondary outcomes include anthropometric, airway, and psychosocial measures. BMI will be evaluated as a continuous variable and categorized using age- and sex-specific CDC percentiles (normal weight, overweight, obese). Mallampati classification (Class I-IV) and Brodsky tonsillar grade (0–4) will be analyzed as ordinal variables.

Psychosocial outcomes include anxiety and depression symptom scores from the RCADS-25, perceived stress scores from the PSS-C, and daytime sleepiness scores from the CRSP-S. For the RCADS-25, both total scores and subscale scores (anxiety, depression) will be examined, with T-scores ≥ 65 indicating borderline clinical significance and ≥70 indicating clinical significance. PSS-C total scores will be analyzed as a continuous variable, with higher scores indicating greater perceived stress. CRSP-S scores will be analyzed as a continuous variable, with higher scores indicating greater daytime sleepiness.

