where $Z_{1-\alpha /2}$ = 1.96 (corresponding to a two-sided significance level of α = 0.05), $Z_{1-\beta }$ = 0.8416 (corresponding to 80% statistical power), and d = 0.80 (Cohen’s d, representing a large standardized effect size). Substituting these values yields$$n=2{\left(\frac{1.96+0.8416}{0.80}\right)}^{2}=2{\left(\frac{2.8016}{0.80}\right)}^{2}=2{\left(3.502\right)}^{2}=2\left(12.264\right)\approx 25\;\mathrm{per}\;\mathrm{group}$$

This yields a minimum of 25 participants per group. Enrollment was set at 30 per group (*N* = 60 total) to accommodate an anticipated attrition rate of approximately 20%, accounting for incomplete recordings, data quality exclusions, and participant withdrawal while preserving adequate statistical power for the primary analysis.

This study is powered to address the primary aim only. Secondary and exploratory analyses are intended to generate preliminary effect size estimates and variability data to inform future hypothesis-driven studies. Up to 300 individuals may be screened to achieve target enrollment, reflecting the expected distribution of risk classification within the clinic population and anticipated exclusions. A stratified quota sampling approach will be used to ensure balanced representation of each PSQ-defined risk group, a design feature that does not alter the cross-sectional nature of the study but ensures adequate statistical power for between-group comparisons. Participants who discontinue or have incomplete data will not be replaced.

The study was approved by the Institutional Review Board of the University of North Carolina (UNC) at Chapel Hill (IRB#25-3218, 26 January 2026) and registered at ClinicalTrials.gov (NCT07581938, 5 May 2026). Recruitment and follow-up procedures will be conducted between May 2026 and June 2027. This protocol is reported in accordance with the Standard Protocol Items: Recommendations for Interventional Trials (SPIRIT) 2025 statement [36] and adapted accordingly for this prospective, cross-sectional observational study. A completed SPIRIT 2025 checklist is provided as Supplementary Table S1.

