### 2.3. Screening and Eligibility

Children meeting all inclusion criteria and none of the exclusion criteria will be eligible for enrollment. The age range of 8–13 years was selected to capture a developmental period when SDB may influence craniofacial growth and psychosocial functioning while also allowing reliable completion of self-report measures.

Eligible participants will be children aged 8–13 years receiving care at the UNC ASOD Pediatric Dentistry Clinic with an American Society of Anesthesiologists (ASA) Physical Status Classification of I or II. Participants must be able to read and understand English or Spanish, provide assent with parental or guardian consent, and have access to a smartphone compatible with the home sleep monitoring application.

Participants will be excluded if they have a prior diagnosis of SDB or OSA, history of adenotonsillectomy, craniofacial syndromes or conditions known to substantially alter craniofacial morphology, prior or current orthodontic treatment, or prior orthognathic surgery. These exclusion criteria were selected to reduce heterogeneity in upper airway anatomy and SDB risk factors that could confound interpretation of physiologic sleep and craniofacial outcomes.

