### 2.6. Clinical and Psychosocial Assessments

Clinical, anthropometric, and psychosocial assessments will be completed during the baseline study visit, prior to initiation of home sleep monitoring. Height and weight will be obtained using standard clinical procedures and used to calculate body mass index (BMI, kg/m^2^). Airway assessments will include the Mallampati classification and Brodsky tonsillar grading scale, both of which have been associated with upper airway obstruction and SDB risk in pediatric populations. Two calibrated examiners will independently perform Mallampati and Brodsky assessments blinded to each other’s scores and to the PSQ results. Discrepancies will be resolved by consensus review. All clinical assessments will be performed by trained study personnel using standardized procedures.

Psychosocial functioning will be assessed using validated self-report instruments administered electronically. Symptoms of anxiety and depression will be measured using the Revised Children’s Anxiety and Depression Scale-Short Version (RCADS-25), a 25-item self-report measure scored on a 4-point Likert scale (0 = never to 3 = always), yielding separate anxiety and depression subscale scores with higher values indicating greater symptom severity [37,38]. Perceived stress will be assessed using the Perceived Stress Scale for Children (PSS-C), a 13-item self-report measure scored on a 4-point Likert scale, with higher total scores reflecting greater perceived stress [39]. Daytime sleepiness will be evaluated using the Sleepiness Scale of the Children’s Report of Sleep Patterns (CRSP-S), a validated self-report measure of daytime sleepiness for school-aged children with demonstrated reliability and construct validity [40].

Detailed administration procedures, scoring algorithms, handling of missing data, interpretation thresholds, and psychometric properties for each psychosocial instrument (RCADS-25, PSS-C, CRSP-S) are provided as Supplementary Materials.

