### 2.9. Statistical Analysis

Descriptive statistics will be used to summarize participant characteristics, clinical measures, psychosocial outcomes, and physiologic sleep parameters. Continuous variables will be reported as means and standard deviations or medians and interquartile ranges depending on distributional characteristics assessed by Shapiro–Wilk tests, while categorical variables will be summarized using frequencies and percentages.

For the primary analysis, physiologic sleep parameters (sAHI, sRDI, SAI, SQI) will be averaged across qualifying recording nights for each participant and compared between PSQ-based risk groups using independent-samples *t*-tests or Mann–Whitney U tests, as appropriate. Night-to-night reliability of physiologic sleep parameters will be assessed using intraclass correlation coefficients (ICCs). Effect sizes will be reported using Cohen’s d and interpreted according to conventional thresholds, with values of approximately 0.20, 0.50, and 0.80 representing small, medium, and large effects, respectively. Sensitivity analyses will be conducted by (1) restricting analyses to participants with three qualifying recording nights; (2) repeating analyses using only the first qualifying night for each participant; and (3) exploring the inclusion of participants with only one qualifying recording night using the single available recording. Multivariable linear regression models will be used to examine associations between SDB risk classification and physiologic sleep measures while adjusting for prespecified covariates including age, sex, and BMI percentile. Additional covariates (asthma, ADHD) will be included if baseline group differences are identified or if they demonstrate meaningful associations with primary outcomes.

Secondary analyses will evaluate associations between SDB risk classification and psychosocial measures (RCADS-25 scores, PSS-C scores, CRSP-S scores) and BMI using linear regression models. Ordinal outcomes (Mallampati classification, Brodsky tonsillar grade) will be analyzed using Mann–Whitney U tests or ordinal logistic regression, as appropriate.

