## 4. Expected Results

This study is designed to characterize associations between questionnaire-based SDB risk classification and physiologic, clinical, and psychosocial measures in a pediatric dental population. Expected outcomes are grounded in the existing literature linking pediatric SDB with adverse sleep, airway, anthropometric, and psychosocial characteristics.

Physiologic Sleep Outcomes. Children classified as high-risk for SDB based on PSQ scores are expected to demonstrate higher AHI, RDI, and SAI values, as well as lower SQI scores, compared with children classified as low-risk. In the original PSQ validation study, the 0.33 threshold on the sleep-related breathing disorder subscale produced a sensitivity of 0.81–0.85 and a specificity of 0.87 for SDB confirmed by PSQ [12]. These findings support the expectation that PSQ-based risk stratification will correspond with objective physiologic differences detected by home sleep monitoring. If these associations are not observed, this may reflect differences in the sensitivity of wearable home monitoring compared with laboratory-based PSG or the influence of night-to-night variability in pediatric sleep parameters.

Airway and Anthropometric Outcomes. Higher SDB risk is expected to be associated with greater BMI, larger tonsillar size as measured by the Brodsky scale, and higher Mallampati classifications. Adenotonsillar hypertrophy is the most commonly recognized risk factor for pediatric SDB, and the prevalence of OSA among children with obesity is estimated at 45% compared with 9% among children with healthy weight, with a 1-unit increase in BMI standard deviation score increasing the odds of OSA by a factor of 1.9 independent of age, sex, and tonsillar hypertrophy [52,53,54,55]. These associations have been demonstrated across diverse pediatric populations and are expected to be replicated within this dental clinic sample.

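### BMI percentile is a poor linear covariate for the adjusted sleep models, and the continuous BMI outcome reads as kg/m² without age and sex standardisation; a BMI-for-age z-score would serve both

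*Protocol article*

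**What the plan says.** BMI appears in the protocol article in two analytic roles and on two continuous scales.

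- **As a covariate.** Section 2.9 fits multivariable linear regressions of the sleep parameters on risk class, "adjusting for prespecified covariates including age, sex, and BMI percentile".
- **As a secondary outcome.** Section 2.6 has height and weight "used to calculate body mass index (BMI, kg/m^2". Section 2.8.2 then states: "BMI will be evaluated as a continuous variable and categorized using age- and sex-specific CDC percentiles (normal weight, overweight, obese". Age and sex standardisation is attached to the categories only. Section 2.9 relates risk class to the psychosocial scores "and BMI using linear regression models", with no covariates listed for these models.

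Three other statements bear on the choice:

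- Section 2.3: "Eligible participants will be children aged 8–13 years".
- Section 2.1: "A stratified quota sampling approach will be used to ensure balanced representation of each PSQ-defined risk group". The quota is defined by PSQ group; age and sex are not mentioned.
- Section 4 expects greater BMI with higher SDB risk. It supports this with "the prevalence of OSA among children with obesity is estimated at 45% compared with 9% among children with healthy weight", and "with a 1-unit increase in BMI standard deviation score increasing the odds of OSA by a factor of 1.9".

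**The concern.** **Covariate.** A percentile is bounded at 100 and flattens in the upper tail. A straight-line term in percentile treats a 5-point step near the median like a 5-point step that spans nearly all of the obese range. Section 4 expects the high-risk group to be the heavier one, so the covariate loses resolution where the groups are expected to differ. If the sleep parameters depend on how far a child lies into that tail, part of the BMI effect stays in the coefficient for risk class. When higher BMI worsens the parameters, that residual points the way the study expects.

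**Outcome.** BMI in kg/m² is generally taken to rise with age over 8–13 years. If one PSQ group happens to be older, the contrast contains an age difference. Section 2.1 wants secondary analyses to supply effect sizes and variability for later studies, and a kg/m² contrast whose SD includes age spread is less useful for that.

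**Working it through.** The documents give no figure for either BMI analysis. The only related figure is the sample size, which reproduces: n = 2 × [(1.96 + 0.8416)/0.80]² = 24.53, so 25 per group. I use 25 below.

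**1. Compression of the percentile scale** (normal distribution only, no trial assumption). Percentile = 100·Φ(z), so the change per unit z is 100·φ(z).

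| z | Percentile | Points per unit z | Relative to median |
|---|---|---|---|
| 0 | 50.0 | 39.9 | 100% |
| 1.645 | 95.0 | 10.3 | 26% |
| 2 | 97.7 | 5.4 | 14% |
| 2.5 | 99.4 | 1.75 | 4% |
| 3 | 99.9 | 0.4 | 1% |

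Two steps of nearly equal percentile length, put on Section 4's scale of 1.9 per SD:

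- 95th to 99.9th: 4.9 points; z from 1.645 to 3.090; 1.9^1.445 = 2.53.
- 50th to 55th: 5.0 points; z from 0 to 0.126; 1.9^0.126 = 1.08.

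These odds ratios show how unequal the steps are. They do not measure bias in the planned models.

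**2. Residual confounding.** This is a large simulation (300,000 per group) with no true group effect. Assumptions, none from the documents: normal BMI z-scores with the means and SDs shown; outcome either 0.5z (linear) or 0.5·exp(0.5z) (steeper at high z), plus noise of SD 1. The entries are the group coefficient, which should be zero.

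| Mean z, low / high risk (SDs) | Outcome shape | Unadjusted | Percentile-adjusted | Share left | Share left with z |
|---|---|---|---|---|---|
| 0.4 / 0.9 (1.1, 1.1) | linear | 0.251 | 0.021 | 9% | −1% |
| 0.4 / 1.4 (1.1, 1.1) | linear | 0.503 | 0.067 | 13% | 0% |
| 0.5 / 1.5 (1.0, 1.2) | linear | 0.500 | 0.114 | 23% | 0% |
| 0.4 / 0.9 (1.1, 1.1) | steeper | 0.203 | 0.040 | 20% | 0% |
| 0.4 / 1.4 (1.1, 1.1) | steeper | 0.458 | 0.126 | 28% | −2% |
| 0.5 / 1.5 (1.0, 1.2) | steeper | 0.538 | 0.222 | 41% | 3% |

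For scale, the standard error of a group difference in noise-SD units with 25 per group is about √(2/25) = 0.28. Under these assumptions the residual bias of 0.02–0.22 is below one standard error.

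**3. Outcome in kg/m².** Assume ages uniform over 8 to just under 14, so SD = 6/√12 = 1.73 years. The standard error of the chance difference in mean age is 1.73 × √(2/25) = 0.49 years. Bias in the BMI contrast = slope × age imbalance. Slopes of 0.3, 0.5 and 0.8 kg/m² per year are assumed.

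- Half-year imbalance: 0.15, 0.25 and 0.40 kg/m².
- One-year imbalance: 0.3, 0.5 and 0.8 kg/m².
- Standard error of the BMI contrast at an assumed within-age SD of 3–5: 3 × 0.283 = 0.85 to 5 × 0.283 = 1.41 kg/m².
- Share of kg/m² variance due to age alone: 1–18%.

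**The case against.** **The kg/m² reading is inferred.** It joins the unit in Section 2.6 to the word continuous in Section 2.8.2, and the covariates of the secondary regressions are simply not listed. A condensed article may leave that list to the analysis plan, and age and sex terms there would largely settle the outcome issue. This stands, so the outcome limb is conditional. It does not reach the covariate, which Section 2.9 states outright.

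**The effects are small.** In the linear scenarios percentile adjustment already removes 77–91% of the confounding. The near-zero result for z partly reflects outcomes generated from z, and nothing in the documents shows that the device measures behave so. A one-year age gap is about a 2-standard-error event, and its bias would still be below the standard error of the BMI contrast. All of this stands and limits the weight of the point.

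**Stronger readings that the documents do not support:**

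- *The primary result is confounded by this choice.* The primary comparison is an unadjusted t-test or Mann–Whitney test; percentile enters only the regression models.
- *2.53 against 1.08 is the size of the bias.* Those odds ratios concern OSA, whereas the planned outcomes are continuous device measures in children with no previous diagnosis.
- *The protocol singles out obesity as the covariate most strongly tied to OSA.* Section 4 ranks no covariates, and its one superlative goes to adenotonsillar hypertrophy.
- *Underweight children are lost.* They have no label in the category list, but they stay in the continuous analysis and no test is named for the categories. This is a minor labelling point.

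**Conclusion.** The point holds in a limited form. The percentile covariate is a stated choice and its compression is a mathematical fact. How much confounding it leaves depends on assumptions: about 9–23% of the unadjusted bias if the outcome is linear in z, and 20–41% if it is steeper at high z, given mean z-scores of 0.4–0.5 in low-risk and 0.9–1.5 in high-risk children. Only the supporting adjusted estimates are affected.

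The outcome issue holds as the text reads, and only if the regression omits age and sex. Its likely size is modest, on a secondary outcome for which the study is not powered. No sample size changes. The change is worth making because it is nearly free and brings the analysis onto the scale of the protocol's own evidence.

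**What to change.** 1. In Section 2.9, replace BMI percentile in the adjusted sleep models with the CDC BMI-for-age z-score, using the extended scale above the 95th percentile.
2. In Sections 2.8.2 and 2.9, name the same z-score as the continuous BMI outcome. Report kg/m² and the percentile categories as description.
3. Add an underweight label to the category list.

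The cost is a small derivation step from height, weight, age and sex, all already collected, plus a wording change. No new data or visits are needed.

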#### 2.8.3. Exploratory Outcomes

Exploratory outcomes include craniofacial and airway-related measurements derived from clinically available lateral cephalometric radiographs. Craniofacial skeletal anterior–posterior, dental anterior–posterior, craniofacial skeletal vertical, dental vertical, and soft tissue profile values are of particular interest due to their relevancy to upper airway patency. These measurements will be summarized descriptively and compared between risk groups. Because imaging is available only for a subset of participants, these analyses are intended to generate preliminary effect size estimates and inform the design of future hypothesis-driven investigations.

### 2.9. Statistical Analysis

Descriptive statistics will be used to summarize participant characteristics, clinical measures, psychosocial outcomes, and physiologic sleep parameters. Continuous variables will be reported as means and standard deviations or medians and interquartile ranges depending on distributional characteristics assessed by Shapiro–Wilk tests, while categorical variables will be summarized using frequencies and percentages.

For the primary analysis, physiologic sleep parameters (sAHI, sRDI, SAI, SQI) will be averaged across qualifying recording nights for each participant and compared between PSQ-based risk groups using independent-samples *t*-tests or Mann–Whitney U tests, as appropriate. Night-to-night reliability of physiologic sleep parameters will be assessed using intraclass correlation coefficients (ICCs). Effect sizes will be reported using Cohen’s d and interpreted according to conventional thresholds, with values of approximately 0.20, 0.50, and 0.80 representing small, medium, and large effects, respectively. Sensitivity analyses will be conducted by (1) restricting analyses to participants with three qualifying recording nights; (2) repeating analyses using only the first qualifying night for each participant; and (3) exploring the inclusion of participants with only one qualifying recording night using the single available recording. Multivariable linear regression models will be used to examine associations between SDB risk classification and physiologic sleep measures while adjusting for prespecified covariates including age, sex, and BMI percentile. Additional covariates (asthma, ADHD) will be included if baseline group differences are identified or if they demonstrate meaningful associations with primary outcomes.

Secondary analyses will evaluate associations between SDB risk classification and psychosocial measures (RCADS-25 scores, PSS-C scores, CRSP-S scores) and BMI using linear regression models. Ordinal outcomes (Mallampati classification, Brodsky tonsillar grade) will be analyzed using Mann–Whitney U tests or ordinal logistic regression, as appropriate.

Exploratory craniofacial analyses will be conducted among the subset of participants with available lateral cephalometric radiographs. Cephalometric measurements will be summarized descriptively and compared between risk groups using independent-samples *t*-tests or Mann–Whitney U tests. Given the anticipated smaller sample size and exploratory nature of these analyses, findings will be reported as effect size estimates with 95% confidence intervals to inform future study design.

No formal adjustment for multiple comparisons will be applied to secondary and exploratory analyses, as these are intended to generate preliminary estimates rather than confirmatory conclusions. All statistical analyses will be performed using SPSS (v. 31, IBM SPSS Statistics, IBM Corp., Armonk, NY, USA). Statistical significance will be evaluated using two-sided tests with an α level of 0.05.

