Pediatric dental providers routinely evaluate craniofacial growth and development, obtain lateral cephalometric radiographs, and assess clinical features such as high-arched palate, tonsillar hypertrophy, mouth breathing, and dental malocclusion—all of which have been associated with SDB risk and fall outside the typical assessment performed at a well-child visit [6,9,10,11]. Fagundes and Flores-Mir (2022) highlighted that specific craniofacial abnormalities frequently identified by dental professionals have been associated with pediatric OSA, and that dental professionals are well positioned to screen for these features because they assess children more frequently than physicians [11]. Additionally, pediatric dental providers have frequent longitudinal contact with children, providing additional touchpoints for screening that do not exist in the medical system and positioning them well to participate in early screening for SDB risk and to help narrow referrals for full medical assessment.

The Pediatric Sleep Questionnaire (PSQ) is a brief, parent-reported instrument that assesses snoring, breathing-related sleep disturbances, and daytime sleepiness. A cutoff score of ≥0.33 has been validated and widely applied in pediatric populations, including school-aged children, to identify those at increased risk for SDB [12,13,14,15,16]. While the PSQ is not intended as a diagnostic tool, this threshold is commonly used for screening and risk stratification to guide referral for further evaluation [17,18]. A growing body of international evidence supports the feasibility and clinical relevance of SDB screening in dental and orthodontic settings. Across eight studies enrolling 4610 children across 14 countries, PSQ-based screening has consistently identified 7–13% of children at risk for SDB, a rate 1.5 to 2.5 times higher than the approximately 5% prevalence reported in healthy general pediatric populations [19,20,21,22,23,24,25]. The convergence across diverse populations, clinical settings, and geographic regions suggests that dental and orthodontic clinics capture a clinically meaningful proportion of children with unrecognized SDB risk. A systematic review of 12 orthodontic-based studies totaling 3737 participants confirmed that SDB risk is consistently elevated in populations with malocclusions and craniofacial risk markers [26].

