### 2.4. PSQ-Based Risk Classification

SDB risk will be assessed using the PSQ, a validated caregiver-completed screening instrument widely used in pediatric research and clinical settings [12]. PSQ scores will be calculated by dividing the number of affirmative responses by the total number of completed items. Participants will be classified as low-risk (PSQ score < 0.33) or high-risk (PSQ score ≥ 0.33) based on the established threshold for pediatric SDB risk stratification. Detailed administration procedures, scoring algorithms, handling of missing data, interpretation thresholds, and psychometric properties for the PSQ are provided as Supplementary Materials [12,37,38,39,40,41,42,43].

The PSQ is used in this study to stratify participants by SDB risk rather than to establish a clinical diagnosis. No diagnostic determinations will be made based on questionnaire responses alone.

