Psychosocial Outcomes. Children classified as high-risk for SDB are expected to demonstrate greater symptoms of anxiety, depression, perceived stress, and daytime sleepiness compared with children classified as low-risk. SDB symptoms have been positively associated with depression, anxiety, attention problems, and reduced adaptability in school-aged children, and a recent meta-analysis estimated an overall 28% prevalence of depression among children with or at high risk for OSA, approximately two-fold higher than among children without OSA [56,57,58]. School-aged children with OSA have also demonstrated significantly higher scores on the Spence Children’s Anxiety Scale and Children’s Depression Inventory compared with controls, with symptom severity correlating with disease duration and hypoxia burden [59]. The inclusion of validated psychosocial instruments in this protocol allows for characterization of these associations within a dental setting where such measures are not routinely collected.

Exploratory Craniofacial Outcomes. Among participants with clinically available lateral cephalometric radiographs, exploratory analyses may identify craniofacial characteristics associated with increased SDB risk. A systematic review and meta-analysis found that children with OSA tend to present with mandibular retrognathia (reduced SNB), increased sagittal skeletal jaw discrepancy (increased ANB), and a steeper mandibular plane angle (increased FH-MP) compared with controls [5]. Additional features described in the literature include increased lower anterior facial height, narrower maxillary arch width, and reduced anteroposterior dimensions of the bony nasopharynx [11,60]. Because radiographs are available only for a subset of participants and are obtained through routine clinical care rather than a standardized research imaging protocol, this subset likely represents an orthodontically indicated subpopulation enriched for skeletal and dental anomalies rather than a random sample of the broader pediatric dental clinic population. Accordingly, cephalometric findings may not be generalizable to all children seen in pediatric dental settings, and between-group differences should be interpreted with this selection bias in mind. These analyses are intended to generate preliminary data and inform future hypothesis-driven investigations.

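### Daytime sleepiness helps define the PSQ risk groups and is then compared between them (CRSP-S), so part of that secondary difference is built in

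*Protocol article*

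**What the plan says.** The Introduction calls the PSQ a "brief, parent-reported instrument that assesses snoring, breathing-related sleep disturbances, and daytime sleepiness". Section 2.4 sets the scoring: "PSQ scores will be calculated by dividing the number of affirmative responses by the total number of completed items". Children are then split at 0.33. No step in the article removes the sleepiness items before the split.

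Section 2.6 names the outcome: "Daytime sleepiness will be evaluated using the Sleepiness Scale of the Children’s Report of Sleep Patterns (CRSP-S), a validated self-report measure of daytime sleepiness". Section 2.8.2 adds that "CRSP-S scores will be analyzed as a continuous variable, with higher scores indicating greater daytime sleepiness". Section 2.9 gives the model: "Secondary analyses will evaluate associations between SDB risk classification and psychosocial measures (RCADS-25 scores, PSS-C scores, CRSP-S scores) and BMI using linear regression models".

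Section 4 (Psychosocial Outcomes) gives the expected direction, with the low-risk group as the comparator: "Children classified as high-risk for SDB are expected to demonstrate greater symptoms of anxiety, depression, perceived stress, and daytime sleepiness compared with children classified as". It supports this with literature on SDB symptoms and OSA. Section 2.1 says the secondary analyses are meant to supply preliminary effect sizes for planning later studies. The limitations in Section 4 discuss the absence of polysomnography, night-to-night variability and selection of the cephalometric subset. They do not mention that the PSQ and the CRSP-S share a construct.

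**The concern.** Sleepiness sits on both sides of the regression. A child who is tired for a reason unrelated to breathing is more likely to collect affirmative PSQ answers, to cross 0.33, and also to score high on the CRSP-S. That child then counts towards an association between SDB risk and sleepiness although breathing played no part. A higher mean CRSP-S in the high-risk group would be expected even if breathing symptoms and sleepiness were unrelated.

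What is at stake is the effect size. The protocol intends to carry it into future study planning, and Section 4 sets it among evidence about disordered breathing. An estimate that contains a built-in part overstates the link with breathing risk, and a larger sample would not remove that part.

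**Working it through.** **Step 1. The structure, from the article alone.**
- Exposure: the PSQ class, a cut at 0.33 of the proportion of affirmative answers over all completed items (Section 2.4). The content includes parent-reported daytime sleepiness (Introduction).
- Outcome: the CRSP-S, child-reported daytime sleepiness (Sections 2.6 and 2.8.2).
- Model: linear regression of outcome on class (Section 2.9).
- Exclusion of sleepiness items from the score: none stated.

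If the parent's sleepiness answers correlate positively with the child's own report, the class carries information about the CRSP-S that does not pass through breathing. This settles the direction but not the size.

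**Step 2. What the article does not give.** It states neither the number of PSQ items, nor how many concern sleepiness, nor endorsement rates, nor the parent-child correlation. It gives no figure for the CRSP-S comparison that could be reproduced. The calculation below is therefore an illustration under assumptions.

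**Step 3. Simulation with no true link between breathing and sleepiness.**
- B (breathing) and S (parent-reported sleepiness) are independent standard normal factors.
- There are 22 binary items, k of them driven by S and 22 − k by B. An item is affirmative when 0.7 × factor + √(1 − 0.7²) × noise exceeds the point that gives 15% endorsement.
- A child is high-risk when the affirmative proportion is at least 0.33.
- Child-reported sleepiness is C = r × S + √(1 − r²) × noise, with r = 0.3 or 0.5.
- d = (mean C in high-risk − mean C in low-risk) / pooled SD, with 400,000 children per setting.
- The rejection rate of a two-sided 5% test with 30 per group comes from the noncentral t distribution with noncentrality d × √(30/2).

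| Sleepiness items of 22 | Spurious d (r = 0.3 to 0.5) | Rejection rate, 30 per group |
|---|---|---|
| 0 | 0.00 | 5.0% |
| 2 | 0.03 to 0.04 | about 5.2 to 5.3% |
| 4 | 0.06 to 0.10 | about 5.6 to 6.7% |
| 7 | 0.14 to 0.24 | about 8 to 15% |

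**Step 4. Other assumptions.** With 20 items, loading 0.6, r from 0.3 to 0.7, and 10% or 30% of children at or above the cut, d was about 0.04 to 0.08 with 2 sleepiness items, 0.08 to 0.20 with 4, and 0.14 to 0.34 with 6. With none it was 0 within simulation error. The sign was the same in every setting that contained sleepiness items.

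**Step 5. Scale.** Section 2.9 calls 0.20 small. With 30 per group the standard error of d near zero is about √(2/30) = 0.26, and the 95% half-width is 1.96 × 0.26 ≈ 0.51. Each spurious d in Step 3 is smaller than one standard error.

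**Step 6. Does removing the items work under quota sampling?** Equal quotas on the full PSQ class could in principle induce a dependence between the remaining items and sleepiness. In the Step 3 settings, reweighted to equal groups, the correlation between the reduced PSQ proportion and C was at most 0.01 in absolute value. The reduced score therefore removes the built-in part almost entirely.

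**The case against.** The strongest reply is that the protocol's target is the association with the PSQ classification itself. Section 2.1 names that as the objective, and Section 2.4 says the PSQ stratifies risk and does not diagnose. That association can be estimated exactly as planned. This stands. A reader might infer that the sleepiness objective cannot be answered as designed, but the documents do not support that. The inflation arises only when the estimate is read as a link between breathing risk and sleepiness. The SDB and OSA literature cited in Section 4 invites that reading.

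Other points also stand in part:
- **Different instruments and informants.** The PSQ comes from the parent and the CRSP-S from the child. This weakens the overlap, and correlations below 1 in the simulation allow for it. It does not remove it.
- **Small size.** With 2 to 4 sleepiness items the spurious difference is well under 0.20. The 7-item setting gives each of the three named domains roughly a third of the items, and naming three domains does not imply equal counts.
- **Unseen scoring detail.** Section 2.4 places scoring algorithms in the Supplementary Materials, and Section 4 ties the 0.33 cut to a breathing-disorder subscale. How many sleepiness items enter the score cannot be settled here, but nothing in the article excludes them.
- **Preliminary status.** The study is powered for the primary aim only. That limits the consequence, although preliminary effect sizes are precisely what this analysis is meant to deliver.

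Two further inferences are not supported. One is that the primary results are compromised: they come from the device and contain no questionnaire items. The other is that further secondary outcomes share PSQ content: the article identifies no such overlap.

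**Conclusion.** The concern holds in limited form. By the article's own description the PSQ class contains parent-reported daytime sleepiness, the CRSP-S comparison tests child-reported daytime sleepiness across that class, and the article neither corrects nor acknowledges this. The direction is clear, provided parent and child reports of sleepiness correlate positively. The size cannot be determined from the article. With 22 items, 15% endorsement, loading 0.7 and a parent-child correlation of 0.3 to 0.5, it is d of about 0.03 to 0.10 with 2 to 4 sleepiness items and 0.14 to 0.24 with 7. It is confined to one preliminary secondary outcome, and the planned association with the PSQ class remains estimable. The point merits a short addition to the plan, not a redesign.

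**What to change.** - Keep the planned regression of CRSP-S on the full PSQ class, and label it as sharing content with the outcome.
- Prespecify beside it a sensitivity analysis of CRSP-S on the PSQ item proportion recomputed without the daytime-sleepiness items, used as a continuous exposure. List the omitted items in advance.
- State in Section 4 that an association seen only with the full class is not evidence linking breathing risk to sleepiness. With 60 children, judge this from estimates and confidence intervals and not from which p-value falls below 0.05.

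The cost is a few lines of text. Section 2.4's scoring already needs the item responses, so no new data or visits are required. The downside is that the reduced score has no validated cutoff. That is why it enters as a continuous exposure and supplements the standard classification without replacing it.
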